### Data Security and Management

The study will be hosted on the servers of Sangath, the implementing organization based in Goa, India. These servers will be encrypted, with data backups occurring daily. The study web portal and its associated data will be accessible only to authorized and approved personnel. When registering, participants will create password-protected accounts and the platform allocates a unique trial IDs to participants. For analyses, data will be deidentified by removing names, contact information, and any other personal identifiers. Students who withdraw from the study will have their data deleted and a withdrawal confirmation notification will be sent from the research team by telephone or email. All data will be stored securely for 10 years.

### Monitoring and Safety

#### Data Monitoring

Monitoring and governance for the pilot trial will be provided by a Trial Steering Committee (TSC; comprising senior investigators and independent subject experts) and Data and Safety Monitoring Committee (DSMC; a fully independent group with relevant clinical and trials expertise). Any study protocol amendments will be agreed and formulated in conjunction with the TSC and DSMC and submitted to relevant institutional review boards for approval.

#### Harms

The study team will continuously monitor for any participant safeguarding concerns. At baseline, all participants will be screened for risk of self-harm or suicide. Risk will be identified using a brief screening questionnaire followed by a telephone-based structured assessment where indicated. If a participant reports the presence of any thoughts of self-harm or suicide during the baseline assessment or during on-boarding or review phone calls (intervention arm participants), a risk management session will be provided to the participant within 24 hours along with information about support services will be immediately provided by the counsellor. If deemed appropriate by the clinical supervisor, the participant will also be referred to an independent mental health specialist for further assessment/treatment. At the 6-week follow-up assessment, all participants will be asked about any negative effects of using the intervention or participation in the study more generally.

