#### Clinical Outcomes

Clinical outcomes will be assessed using 2 validated self-report questionnaires that measure psychosocial problem severity (Youth Top Problems [YTP]) [26] and self-reported depression and anxiety (Revised Child Anxiety and Depression Scale–Short Version [RCADS-25]) [27]. Assessments will be carried out at two timepoints: prerandomization at baseline and postintervention follow up (6 weeks after randomization). Measures will be collected on the internet through the study website.

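### After randomization, the only named occasions for a self-harm report are calls that the intervention arm alone receives, so counts of such reports by arm would not be comparable

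*Protocol article*

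**What the plan says.** The Harms section makes four provisions.

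- A general one: "The study team will continuously monitor for any participant safeguarding concerns". No method is given.
- A screen before randomization: "At baseline, all participants will be screened for risk of self-harm or suicide". It is a brief questionnaire, followed by a structured telephone assessment where indicated.
- A response to reported self-harm or suicidal thoughts, with the occasions named: "during the baseline assessment or during on-boarding or review phone calls (intervention arm participants), a risk management session will be provided". The restriction to the intervention arm is the protocol's own.
- A question at 6 weeks: "all participants will be asked about any negative effects of using the intervention or participation in the study more generally".

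Clinical Outcomes times the two assessments as "prerandomization at baseline and postintervention follow up (6 weeks after randomization") and names YTP and RCADS-25 as the measures. Control Arm describes a digital flyer with service and helpline details. The Discussion adds that the choice of control rules out the same counsellors dealing with both arms. Statistical Analysis is mainly descriptive and states no between-arm comparison of harms.

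**The concern.** After randomization the chance that a self-harm thought is recorded depends on the arm. Intervention students have two scheduled counsellor calls, and may have proactive calls for non-use (Counsellors) and on-demand support calls (Delivery). Controls have no scheduled counsellor contact. A count by arm then mixes the risk of an event with the opportunity to disclose it.

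Three things are at stake. The DSMC could misread a raw table as a signal against the intervention. An apparently quiet control arm could be taken as reassurance when it reflects fewer occasions to report. And a pilot meant to test research procedures would hand an arm-dependent harms procedure to the full-scale trial. No later analysis can recover reports that were never elicited from controls.

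**Working it through.** The protocol gives no harms rate and no harms comparison, so there is no figure to reproduce. The check has two parts.

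**1. Routes by arm after randomization**

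| Route | Section | Intervention | Control | Specific to self-harm? |
|---|---|---|---|---|
| On-boarding and review calls | Delivery; Harms | Yes | No | Named as occasions for a report; not said to screen |
| Proactive and on-demand counsellor calls | Counsellors; Delivery | Yes, as needed | None described | No |
| Continuous safeguarding monitoring | Harms | Yes | Yes | No; method not stated |
| Researcher calls (allocation, follow-up reminder) | Allocation and Randomization; Follow-up Assessment | Yes | Yes | No risk enquiry described |
| 6-week negative-effects question | Harms | Yes | Yes | No; about the intervention or participation |
| YTP and RCADS-25 at 6 weeks | Clinical Outcomes | Yes | Yes | No self-harm item described |

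The routes open to both arms are general. The only ones tied by name to a self-harm report are in one arm. A smaller asymmetry runs the same way: under Feasibility Outcomes, potential harms are among the extra interview topics for intervention-arm participants, within a purposive subsample of about 10 to 15 drawn from both arms.

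**2. Size, for illustration**

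From the protocol: 35 per arm (Sample Size). Assumed, because the protocol gives neither:

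- true risk p of new self-harm thoughts, equal in both arms: 3%, 5% or 10%;
- probability that a case is recorded: s1 = 0.8 in the intervention arm; s0 = 0 in controls, or 0.3 if the general routes pick up some cases.

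Expected recorded cases per arm = 35 × p × s. Spurious excess = p × (s1 − s0).

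| p | s1 v s0 | Expected recorded cases | Difference (cases) | Excess (percentage points) |
|---|---|---|---|---|
| 3% | 0.8 v 0 | 0.840 v 0 | 0.840 | 2.4 |
| 3% | 0.8 v 0.3 | 0.840 v 0.315 | 0.525 | 1.5 |
| 5% | 0.8 v 0 | 1.400 v 0 | 1.400 | 4.0 |
| 5% | 0.8 v 0.3 | 1.400 v 0.525 | 0.875 | 2.5 |
| 10% | 0.8 v 0 | 2.800 v 0 | 2.800 | 8.0 |
| 10% | 0.8 v 0.3 | 2.800 v 1.050 | 1.750 | 5.0 |

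Worked line: 35 × 0.03 × 0.8 = 0.84 and 35 × 0.03 × 0.3 = 0.315; the excess is 0.03 × (0.8 − 0.3) = 1.5 points. With the same enquiry in both arms (0.8 v 0.8) the spurious difference is 0 at every p.

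**The case against.** A reader might infer that self-harm risk among controls goes unrecorded, or that the trial's harms comparison is biased by design. The documents support neither.

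- Two provisions in the same section cover controls: the continuous monitoring and the 6-week question. Under-ascertainment is likely; complete non-recording is not established.
- The protocol promises no between-arm comparison of harms and no self-harm event rate. The bias attaches to such a table if one is made, not to a stated analysis. The 6-week question itself goes to both arms at the same time.
- The text describes what follows if a participant reports such thoughts. It does not say that the calls screen for them, so the two calls are scheduled contacts and not structured enquiries.
- The article is condensed. The baseline risk screen is itself missing from the schedule in Table 2, so that table's silence does not prove that no screen takes place at 6 weeks, and the exact wording of the negative-effects item is not shown.
- Incidence and detection are assumptions. Students with elevated risk requiring external referral are excluded at entry (Eligibility Criteria), so the true rate could be low. At 3% risk and 0.3 control detection the expected counts are 0.84 v 0.32, which a single pilot could not show.

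All of this limits the claim. What it leaves standing is explicit text, not silence: the protocol lists the occasions, marks the post-randomization ones as intervention-arm, and describes nothing specific to self-harm that controls would share.

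**Conclusion.** The point holds as one of unequal ascertainment. Followed as written, the plan makes the recording of self-harm reports after randomization depend on the arm, and the general both-arm provisions do not restore balance. Any tabulation of self-harm or safeguarding reports by arm would tend to show more in the intervention arm at equal true risk. The direction rests on detection being better where counsellor calls take place. The size is unknown: the range of 1.5 to 8 percentage points (0.525 to 2.8 cases of 35) depends entirely on the assumed risk and detection values. It is worth correcting because the reporting remedy is nearly free and because a full-scale trial could inherit the procedure.

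**What to change.** 1. **Reporting.** State that arms are compared on harms only with items collected identically at 6 weeks: the negative-effects question, and the number per arm who worsened from baseline on RCADS-25 and on YTP, with worsening defined before data are seen by arm. Show how many in each arm answered. List reports that arose in counsellor calls separately, by route, with no between-arm comparison and a note that controls had no such calls. The cost is analysis wording; the scores are already collected.

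2. **Measurement, as a cheap improvement.** Repeat the baseline risk screening questionnaire in the 6-week online assessment in both arms and use it as the symmetric safety measure. Responses would be handled under whatever procedure the trial already has; this point takes no view on that procedure. The cost is a few items on an existing form, some additional responses to handle, and an amendment that the Data Monitoring section requires to be agreed with the TSC and DSMC and submitted for review board approval. The Results section says that participants are already completing follow-up, so the item would reach only the remaining follow-ups. If that is too few to be useful, it should be carried into the full-scale trial.

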#### Control Arm

Through the study website, participants will be sent a digital flyer consisting of information and contact details about local mental health service providers and 2 recently established government provided/affiliated helplines [23,24].

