#### Feasibility Outcomes

Feasibility of research procedures will be assessed through routinely logged numbers and proportions of eligible/ineligible self-referrals (with reasons for ineligibility), assenting/consenting participants (with reasons for not assenting/consenting), randomized participants (with reasons for not randomizing), and completed outcome assessments (with reasons for noncompletion).

Feasibility of the intervention delivery will be assessed using data on attendance, intervention completion (ie, attendance at on-boarding and review telephone calls and use of the POD Adventures app) and counsellor-completed fidelity checklists of on-boarding and review discussions.

Intervention processes will be assessed through the number and duration of contacts with counsellors, number of days between on-boarding and review sessions, amount of app content completion, and reasons for non-completion. Data about participants’ use of the app will also be captured securely from integrated analytics software. Key indicators will include login and logout timestamps, knowledge of problem-solving assessed through multiple-choice quizzes, and self-reported use of problem solving in real-world situations.

User satisfaction data will be obtained from participants in the intervention arm at 6 weeks using an 8-item service satisfaction questionnaire [25] with 4 appended forced-choice items that ask specifically about the experience of using the POD Adventures app.

After the follow-up assessment, semistructured qualitative interviews will be conducted with approximately 10-15 participants sampled purposively in accordance with sex and age from both study arms; the exact number of interview participants will depend on thematic saturation. Interviews will be carried out over the telephone by a researcher who has not been involved in intervention delivery. Participants will be asked about their experiences of internet-based research procedures such as recruitment, use of the study website, consent, and assessment procedures. Intervention arm participants will be asked additional questions about acceptability of using the intervention on the internet, their experiences of guidance from counsellors, usability and utility of app features, and potential harms. Interviews will be audio-recorded and transcribed by a member of the study team.

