### Analyses

#### Statistical Analysis

The statistical analysis for this pilot trial will be mainly descriptive in nature, aiming to provide estimates of key trial parameters and to inform power calculations for a future trial. The outcome measures will be summarized at baseline and at 6-week follow up by trial arm. These will be summarized by mean (SD), median (IQR), or n (%) values as appropriate to relevant subgroups (defined by age, gender, and baseline outcome score). For continuous outcomes, histograms will also be plotted within each arm to assess normality and whether any transformation is required.

Analyses will be conducted to examine the effect of the intervention in normal and clinical subgroups (as measured by the RCADS-25).

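### After randomization, the only harms question specified for both arms asks about effects of the intervention or of taking part, so solicited harms are not validly comparable between arms

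*Protocol article*

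**What the plan says.** All references are to the protocol article.

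- **Harms, at 6 weeks, both arms:** "all participants will be asked about any negative effects of using the intervention or participation in the study more generally".
- **Harms, at baseline, both arms:** "At baseline, all participants will be screened for risk of self-harm or suicide". No repeat of this screen is described.
- **Harms, between baseline and 6 weeks:** thoughts of self-harm or suicide may also come to light "during on-boarding or review phone calls (intervention arm participants"). Separately, "The study team will continuously monitor for any participant safeguarding concerns", with no instrument or schedule given.
- **Control Arm:** "participants will be sent a digital flyer consisting of information and contact details about local mental health service providers", together with details of two helplines. The Delivery and Counsellors sections give the other arm an app for 4 weeks, an on-boarding call, a review call, weekly text messages, and calls to those who do not use the app.
- **Feasibility Outcomes, interviews:** "Intervention arm participants will be asked additional questions about acceptability of using the intervention on the internet". Potential harms are the last topic in that intervention-only list.
- **Clinical Outcomes:** YTP and RCADS-25 are completed in both arms before randomization and at 6 weeks.
- **Statistical Analysis:** "The outcome measures will be summarized at baseline and at 6-week follow up by trial arm". Means, medians or counts are planned as appropriate, with histograms by arm and subgroups that include baseline score.

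**The concern.** A fair comparison of harms needs the same event to have the same chance of being recorded in each arm. A question about effects of something asks the respondent to judge cause before reporting. An intervention student whose mood falls has an app, a counsellor and reminders to connect it with. A control student who was sent a flyer has little beyond the assessments. Equal worsening can therefore produce unequal reports.

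The pilot exists to test research procedures for a full-scale trial. If this way of asking is carried forward, the larger trial inherits it, and its oversight committees would read a difference in reporting as a difference in harm. In the other direction, worsening that no student links to the study would not be solicited in either arm. The outcome scales could supply a count that needs no attribution, but the analysis section does not name one.

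**Working it through.** **The plan's own figure.** The only relevant figure is the sample size of 70, 35 per arm, chosen for precision of a standard deviation. No confidence level or target width is stated, so 70 cannot be derived from the article. The point does not depend on it.

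**Step 1. Harms routes side by side.**

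| Route | Intervention | Control | Free of attribution? |
|---|---|---|---|
| Self-harm/suicide screen, baseline | yes | yes | yes, but before randomization |
| On-boarding and review calls | yes | no | yes |
| Interview questions on harms | yes (subsample) | no | not stated |
| Continuous safeguarding monitoring | yes | yes | no instrument or schedule stated |
| 6-week question on negative effects | yes | yes | no |

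After randomization, each route with stated content either exists in the intervention arm only or asks about effects of the intervention or of taking part.

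**Step 2. What attribution does to the comparison.** Let d be the true proportion who worsen, equal in both arms. Let a_I and a_C be the chances that a worsened student reports it as an effect of the intervention or study. Then

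reported difference = d × a_I − d × a_C = d × (a_I − a_C).

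This is zero only if a_I = a_C. In principle it can lie anywhere from −d to +d. A positive value is expected, because controls have less to attribute to. The document gives none of the three quantities, so no single size can be defended.

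**Step 3. Do the planned score summaries show worsening?** Only indirectly. Summaries at two separate timepoints do not show who moved, because students who improve and students who worsen offset each other. As an illustration, assume normal change scores with a mean improvement of 0.3 SD. The share worsening by at least 0.5 SD is 1 − Φ((0.5 + 0.3)/s), where s is the SD of change in the same units:

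- s = 0.8: 1 − Φ(1.00) = 15.9%
- s = 1.0: 1 − Φ(0.80) = 21.2%
- s = 1.2: 1 − Φ(0.67) = 25.2%

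An average improvement is thus compatible with an appreciable share who worsen. The paired data needed to count them are already collected.

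**Step 4. What a by-arm count could deliver.** The 95% half-width for a difference in proportions is 1.96 × √(2p(1 − p)/n). The rates p are assumptions, and 28 per arm assumes 20% loss.

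| p | n = 35 per arm | n = 28 per arm |
|---|---|---|
| 5% | 10.2 points | 11.4 points |
| 10% | 14.1 points | 15.7 points |
| 20% | 18.7 points | 21.0 points |

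The count would be symmetric between arms but imprecise.

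**The case against.** The strongest reply has four parts.

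1. **The article describes a topic, not the item.** The verbatim wording may sit in a form that is not shown. This stands as a caution. But the content the article does fix is effects of the intervention or of participation, and that is the content at issue. Extending it to participation gives control students something to answer. It does not make their answers equivalent.

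2. **Comparing harms is not a stated aim, and the analysis is mainly descriptive.** This is true, and it limits the weight of the point. It does not remove it, because testing research procedures is an aim.

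3. **A deterioration table is commonly left to the analysis plan.** This is also true, so its absence alone would be no finding. It enters here as the available remedy for an asymmetry that the Harms section itself creates.

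4. **A small pilot cannot settle which arm leaves more students worse off.** Agreed: the half-widths show it. Small numbers are a separate matter from bias. With no events among 35 students the two-sided 95% upper limit is 1 − 0.025^(1/35) = 10.0%, however the question is worded.

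Some stronger readings are tempting and are not supported:

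- A reader might infer that worsening is hidden in means. The Statistical Analysis section also plans medians, counts, histograms by arm and subgroups by baseline score.
- A reader might take the harms question to be part of the online form. The statement "Measures will be collected on the internet through the study website" concerns the clinical questionnaires, and the Harms section gives no mode.
- A reader might conclude that harms cannot be compared at all. Both scales are collected in both arms at both timepoints, so worsening can be derived.
- A reader might say that reported harms must be higher in the intervention arm. That direction is expected, not guaranteed.

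**Conclusion.** The point holds as a matter of unequal ascertainment. The 6-week question is the only harms question specified for both arms after randomization. It depends on attribution, and the arms differ sharply in what there is to attribute to. The baseline screen comes too early to repair this, and safeguarding monitoring has no stated instrument or schedule. Solicited harms, as the article fixes them, are not validly comparable between arms.

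No figure in the document is wrong, and the size of the bias cannot be computed from it. It equals d × (a_I − a_C), with all three terms unknown. The conclusion assumes that the item follows the content described in the Harms section and that students with less exposure attribute less. The feasibility objectives and the estimates for the sample size calculation are not affected. The change is worth making because it is cheap and because the full trial would otherwise inherit the procedure.

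**What to change.** 1. **Harms section.** Reword the 6-week question so that both arms are asked, in identical words, about any new or worsened problem since joining, with attribution to the intervention or the study asked second. The article reports follow-up already under way. For participants already followed up, report the date of the change, or carry the new wording into the full trial.

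2. **Statistical Analysis section.** Add one descriptive table by arm with the number and proportion of students who worsen from baseline to 6 weeks on RCADS-25 and on YTP. Fix the thresholds before unblinded data are seen. Set them beyond measurement noise, so that not every small rise counts. Define them so that students already in the clinical range at baseline can also be counted as worsened, which a move from normal to clinical alone would miss.

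**Cost.** The first change is to wording and will bring in more non-specific reports. The second is one table from data already held. Its intervals will be wide at 35 per arm, so it should be labelled as descriptive, with no test of a difference.

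Putting the question to non-completers during the follow-up calls is not needed for this point. It could reveal allocation to researchers whom the Allocation and Randomization section keeps blind.

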#### COVID-19 Precautions

The research team will implement the pilot trial in line with local and national public health guidance and make every effort to minimize in-person visits to schools unless specifically requested by schools. Health and safety measures outlined in local government guidelines for school reopening will be strictly followed by research staff who may visit schools as part of any recruitment activities. In addition, fieldwork safety training will be provided to all study team members. Study team members will employ measures to maintain physical distancing and use of personal protective equipment such as masks in line with local health and safety protocols.

